**Conclusions:**

This trial will contribute to examining mindfulness-based interventions, delivered via the web, for improving current, residual, or chronic depression symptoms. It will (1) address the feasibility of MBCT delivered via the web; (2) contribute evidence regarding MBCT’s efficacy in reducing depression symptoms and psychiatric distress; and (3) assess the impact of MBCT on several important secondary outcomes. Findings from this study will develop the understanding of the causal pathways between MBCT delivered via the web and depression symptoms further, elucidating the potential for future larger-scale designs.

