### Sample Size

The total sample size of our trial is expected to be 128 individuals with 64 participants placed into each group. This was estimated by a 2-tailed *t* test using GPower 3.1 (Informer Technologies, Inc) software. Our calculation of sample size depended on (1) the level of significance (α error probability), which was set as .05 based on Ronald A Fisher’s suggestion [55]; (2) the expected effect size, which was set as *d*=0.5, according to Cohen classification that “a medium effect of .5 is visible to the naked eye of a careful observer” [56]; (3) the expected power of this study (1–β error probability), which was set as 0.8 based on Cohen theory [57] because we failed to obtain support from previous similar studies; and (4) the allocation ratio (N2/N1), for which we expect number of participant in treatment group and control group to be the same.

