#### Secondary Outcomes, Moderators, and Mediators

GLMMs will be used to assess the association between MBCT and the secondary outcomes of perceived stress and mindfulness skills (hypothesis 4). Potential moderators of the effect of MBCT, namely treatment history, traumatic life events history, baseline depression, and their interaction with MBCT, will be looked at in their own GLMMs. Using regression coefficients, the role of moderators that these variables may play will be assessed.

Using the PROCESS macro [59] in SAS (SAS Institute), the mediators, extent of mindfulness self-practice, and executive functioning skills (hypothesis 5), will be examined via the product of the coefficient method. This will be limited to the first phase of this study lasting 8 weeks. Further, 2 separate GLMMs will be used to assess how the primary and secondary outcomes may be indirectly influenced by MBCT. By regressing the mediator and outcome, respectively, on MBCT, and controlling for the mediators as well as applicable covariates, the indirect effects of MBCT on outcomes will be examined. Parallel multiple mediator models in addition to serial multiple mediator models will be used to conduct sensitivity analysis. To examine if MBCT effects will be sustained through 8 weeks postintervention (hypothesis 3), linear mixed-effects models will be used with main effects consisting of treatment group, time, group × time interaction, and nested random effects for subjects and cluster. A regression parameter associated with group × time interaction at 0 will be the null hypothesis. This acts as an equivalent for assessing the carryover effect [60]. If rejected, there is support that the effects of the intervention remain after 8 weeks have elapsed. An imputation method will be used to address any data that are missing.

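### The named mediation sensitivity analysis checks omission of the other measured mediator, not unmeasured mediator-outcome confounding, on which the causal reading of hypothesis 5 rests

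*Protocol article*

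**What the plan says.** The Statistical Methods subsection on secondary outcomes, moderators and mediators examines two mediators, self-practice in days per week and self-reported executive functioning. It uses the product of coefficients and is restricted to the first 8-week phase. The outcome model is described as "controlling for the mediators as well as applicable covariates, the indirect effects of MBCT on outcomes will be examined". The one sensitivity analysis named for mediation is: "Parallel multiple mediator models in addition to serial multiple mediator models will be used to conduct sensitivity analysis".

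The subsection on primary outcomes adds baseline (TI) covariates that are relevant and unbalanced between arms to all models. Neither subsection names the TI mediator or TI outcome as a fixed covariate for hypothesis 5.

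The abstract's Conclusions state: "Findings from this study will develop the understanding of the causal pathways between MBCT delivered via the web and depression symptoms further". The Principal Findings section of the Discussion expresses the same hope for self-practice and executive functioning.

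**The concern.** Arm is randomised; the mediators are not. Participants choose how much to practise, and executive functioning is self-reported alongside self-reported, unblinded outcomes. The arm-to-mediator path is protected by randomisation. The mediator-to-outcome path has a causal meaning only if no unmeasured factor, such as motivation, response style, life events or a change in usual care, moves both.

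Parallel and serial models keep this assumption. Both use the same outcome equation (outcome on arm, mediator 1 and mediator 2), so the mediator-to-outcome coefficients are identical in the two. For the mediator placed first in the chain, the whole specific indirect effect is identical. For that effect the two models amount to one re-test, and it does not touch the assumption in doubt.

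At stake is the reading of hypothesis 5. An indirect effect produced by confounding could be reported as robust because the extra models agree with it.

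**Working it through.** **Inputs from the article (Sample Size).** "The total sample size of our trial is expected to be 128 individuals with 64 participants placed into each group"; significance level "which was set as .05"; "This was estimated by a 2-tailed" t test; effect size "which was set as *d*=0.5"; power "which was set as 0.8 based on Cohen theory".

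**The plan's own figure.** A two-sided two-sample t test with d = 0.5 and 64 per arm has power 0.8015, so 128 reproduces. No figure is given for mediation.

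**Assumptions.** MBCT shifts mediator and outcome by 0.5 SD each. The mediator has no effect on the outcome. Confounding appears as a residual mediator-outcome correlation ρ. Ordinary regression is used without clustering. The indirect effect counts as significant when both paths have p < .05, standing in for the product-of-coefficients test.

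**Step 1: when the mediator-to-outcome path is significant.** With 125 degrees of freedom the critical t is 1.979. The smallest significant partial correlation is 1.979/√(1.979² + 125) = 0.174. An unmeasured factor correlated √0.174 = 0.42 with both mediator and outcome is enough to produce it.

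**Step 2: false single-mediator finding.** The arm-to-mediator path is significant with probability 0.80. By Fisher's z, the second path is significant with probability about Φ([atanh ρ − atanh 0.174]·√124), where √124 = 11.14 and atanh 0.174 = 0.176.

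- ρ = .2: Φ((0.203 − 0.176) × 11.14) = Φ(0.30) = 0.62; × 0.80 = 0.49
- ρ = .3: Φ((0.310 − 0.176) × 11.14) = Φ(1.49) = 0.93; × 0.80 = 0.75
- ρ = .4: Φ((0.424 − 0.176) × 11.14) = Φ(2.76) ≈ 1.00; × 0.80 = 0.80

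Simulation (3,000 to 4,000 runs) gives 4%, 16%, 49%, 74% and 79% at ρ = 0, .1, .2, .3 and .4.

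**Step 3: does the joint model expose it?** Let r be the residual correlation of each mediator with the outcome, and q the correlation between the mediators. After adjusting for mediator 2, the partial correlation of mediator 1 with the outcome is (r − rq)/√[(1 − q²)(1 − r²)]. At r = .2 this is 0.167 for q = .2 and 0.118 for q = .5. It shrinks but does not vanish. The share of false findings repeated for the same mediator is:

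| Set-up | r = .2 | r = .3 | r = .4 |
|---|---|---|---|
| q equal to r | 75% | 79% | 90% |
| q = .5 | 43% | 57% | 83% |

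A second simulation (6,000 runs; MBCT effects 0.8 and 0.5 SD on the two mediators) used an explicit confounder with loading 0.3 to 0.7 on mediator 1 and on the outcome. The share repeated was 95% to 100% when it acted on one mediator only, and 75% to 97% when it acted equally on both.

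**Step 4: what the remedies do.**

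- *TI adjustment, stable traits only* (60% of variance, trait correlation .5): false mediation falls from about 75% to about 14%.
- *TI adjustment, with a correlation of .3 in the time-varying part as well*: no protection, 81% unadjusted against 83% adjusted. A variant with that correlation at both time points gave 80% against 91%, partly because adjustment also sharpens the arm-to-mediator path.
- *Varying ρ*: evaluated at the true residual correlation (0.16, 0.25 or 0.49 in size), the false rate is 4.7%, 4.9% and 4.8%.

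**The case against.** **Purpose.** The article does not say that the parallel and serial models are meant to probe unmeasured confounding. With two mediators, checking a single-mediator result against joint models is a legitimate specification check. This stands: the models should be kept. It does not answer the point, because the causal reading depends on an assumption that the named check leaves fixed.

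**Size.** A reader might infer that the joint models nearly always confirm a false effect, or that the check cannot fail. The documents do not support that. They give no mediator correlations, and under plausible values the same false effect is often not repeated (43% to 57% with mediators correlated .5 and r of .2 to .3). What can be said is that the repetition rate depends on how mediators and confounder are related, so neither agreement nor disagreement tests the assumption.

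**Covariates.** A reader might also infer that hypothesis 5 covariates are selected only by arm imbalance. The primary-outcomes subsection adds unbalanced covariates but does not limit models to them, and the mediation subsection leaves its own covariates undefined. The full protocol or SAP may specify them, and may add a confounding analysis. What stands is that balance between arms is no guide here: a perfectly balanced TI score can still confound the mediator-outcome path.

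**Value of TI adjustment.** Entrants must have no current mindfulness practice, so TI self-practice should be close to zero and adjusting for it does little. This stands; among the mediators the gain is mainly for executive functioning.

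**Model.** The planned models are mixed models, whereas the simulation uses ordinary regression. The percentages are therefore illustrative. The structural argument does not depend on them.

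**Conclusion.** The point holds in this form: the mediation sensitivity analysis named in the article tests dependence on the other measured mediator and leaves the assumption of no unmeasured mediator-outcome confounding untested. A causal reading of hypothesis 5 would therefore rest on an unexamined assumption. At 128 participants a residual correlation of 0.174 is enough to create a just-significant mediator path.

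The 49% to 79% and 43% to nearly 100% ranges hold under the assumed correlations and MBCT effects above, not under anything the article states. The finding is of moderate weight. The mediators are labelled as possible ones, the causal language is partly hedged, and the week-8 primary comparison and the sample size of 128 are unaffected.

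**What to change.** In the mediation paragraph of the Statistical Methods:

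1. Include the TI value of the outcome and of executive functioning (and of self-practice where it varies) as fixed covariates in both hypothesis 5 regressions, regardless of arm balance. State that this helps only against confounding by stable traits.
2. Add a sensitivity analysis that varies the residual mediator-outcome correlation, for example from −0.5 to 0.5, and reports the value at which the indirect effect vanishes.
3. Describe the parallel and serial models as alternative specifications.

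The cost is a little more analysis code. The PHQ-9 is stated to be measured at baseline. TI collection of the mediators is implied by the three assessment points, but should be confirmed against the schedule in Figure 2, which was not available here. The mediation claim will usually come out weaker.

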## Methods

### Study Design

Our study plans to examine how MBCT delivered via the web may affect primary and secondary outcomes for individuals with a history of depression. It will also assess mediators, moderators, and the sustainability of the intervention. The following hypotheses will be assessed among program participants in the intervention group as compared to a waitlist control group, and within groups compared from pre- to postintervention.

The MBCT intervention group will show a greater reduction in depressive symptoms from TI to TII, compared to the waitlist group.The MBCT intervention group will show a greater reduction in psychiatric distress symptoms from TI to TII compared to the waitlist group.The MBCT intervention group will sustain gains through the 8-week follow-up period at TIII.The MBCT intervention will improve secondary outcomes, such as:perceived stressfacets of mindfulnessThe MBCT intervention will improve the skills associated with mechanisms of change for individuals with a history of depression, and these skills will act as mediators between MBCT and primary and secondary outcomes:extent of mindfulness self-practiceexecutive functioning skillsThe format delivered via the web will meet feasibility aims measured by adherence, retention, attendance, and engagement.

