### Trial Design

Using a waitlist control design, this trial will randomize 128 eligible participants into 2 groups. In the first phase lasting 8 weeks, group 1 will partake in the MBCT intervention plus treatment as usual (MBCT + TAU) while group 2 will remain as waitlist control following TAU. In the second phase lasting 8 weeks, group 2 will begin completing the MBCT intervention, and group 1 will enter a follow-up phase, continuing with TAU. TAU will be comprised of psychotherapy, pharmacotherapy, or a combination of both. Data collection will be completed at baseline, 8 weeks (postintervention for group 1 and preintervention for group 2), and 16 weeks (follow-up for group 1 and postintervention for group 2). In this manner, our study design will ensure that both trial arms are treated fairly, and that group 1 can be followed up for 8 weeks to assess the sustainability of the intervention. Figure 1 outlines the flow of this study. The registration of this trial took place on April 22, 2022.

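### The rule for hypothesis 3 takes a rejected group × time interaction as support for lasting effects, but group 2 has MBCT before TIII, so on the natural reading rejection does not indicate that gains were kept

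*Protocol article*

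**What the plan says.** Under Study Design, hypothesis 3 reads: "The MBCT intervention group will sustain gains through the 8-week follow-up period at TIII". It concerns group 1 only, and the period from TII (week 8) to TIII (week 16).

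Trial Design says what group 2 does in that period: "group 2 will begin completing the MBCT intervention, and group 1 will enter a follow-up phase, continuing with TAU". The week-16 visit is accordingly described as "16 weeks (follow-up for group 1 and postintervention for group 2").

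Secondary Outcomes, Moderators, and Mediators gives the test: "linear mixed-effects models will be used with main effects consisting of treatment group, time, group × time interaction", with nested random effects for subject and cluster. The null is then stated: "A regression parameter associated with group × time interaction at 0 will be the null hypothesis". Two interpretive sentences follow: "This acts as an equivalent for assessing the carryover effect" and "If rejected, there is support that the effects of the intervention remain after 8 weeks have elapsed".

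The section names no direction, does not say which visits the interaction compares, and gives no estimate of change within group 1. The Primary Outcomes section also assigns hypothesis 3 to mixed models, without naming a contrast.

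**The concern.** A group × time interaction asks whether the two arms changed differently. Between TI and TII that is the right question, because one arm has MBCT and the other does not. By TIII both arms have had it. If the programme works equally well in both and group 1 keeps its gain, the arms end at the same level, and the overall TI-to-TIII interaction is zero in exactly the case the hypothesis hopes for. If group 1 relapses, the arms separate and the interaction is rejected. Between TII and TIII the interaction is non-zero simply because group 2 is being treated, and it grows if group 1 worsens.

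Sustainability is one of the reasons Trial Design gives for following group 1, and the Discussion presents it as a contribution to the literature. A rule that is satisfied more readily when gains are lost could turn that conclusion round.

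**Working it through.** **Inputs from the Sample Size section.** 128 participants, 64 per arm; two-sided α = 0.05; standardised effect d = 0.5; power 0.80.

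**The plan's own figure.** An exact two-sample t calculation with d = 0.5, α = 0.05 and power 0.80 gives 63.77, so 64 per arm and 128 in total, with power 0.801. The sample size reproduces and is not at issue.

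**Assumptions, because the article gives no figures.** Outcome SD 1 at every visit; equal correlation ρ between visits (0.5, range 0.3 to 0.7); complete data; no allowance for clustering within therapy groups. Let s be the share of its gain that group 1 keeps at TIII, and g the gain of group 2 from MBCT relative to that of group 1. Time trends common to both arms cancel.

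**Expected means (TI, TII, TIII; lower is better).**
- Group 1: 0, −d, −s·d
- Group 2: 0, 0, −g·d

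**Interaction contrasts with group as randomised arm (group 1 change minus group 2 change).**
- TI to TIII: −s·d + g·d = d(g − s)
- TII to TIII: (d − s·d) + g·d = d(1 + g − s)
- TI to TII: −d, whatever s is, so it says nothing about maintenance

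**Standard error.** The SD of a change is √(2(1 − ρ)), which is 1 at ρ = 0.5. The standard error of the difference between arms is 1 × √(2/64) = 0.177.

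**Chance of rejection at g = 1, ρ = 0.5** (noncentral t; noncentral chi-square for the joint test):

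| Contrast | Gains kept (s = 1) | Half lost (s = 0.5) | Fully lost (s = 0) |
|---|---|---|---|
| TI to TIII: size | 0 | 0.25 | 0.50 |
| TI to TIII: rejected | 5% | 29% | 80% |
| TII to TIII: size | 0.50 | 0.75 | 1.00 |
| TII to TIII: rejected | 80% | 99% | >99% |
| Joint test, 2 df: rejected | 84% | 98% | >99% |

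A simulation of 5,000 trials at ρ = 0.5 agreed for the single-contrast tests (TI to TIII: 4.8%, 28.8% and 79.8%).

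**Range over ρ = 0.3 to 0.7.** TI to TIII is rejected 5% of the time if gains are kept and 66% to 95% if they are lost. TII to TIII is rejected 66% to 95% if kept and over 99% if lost.

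**Dependence on g.** For TI to TIII the contrast is d(g − 1) if gains are kept and d·g if they are lost. The second is larger in absolute size only when g > 0.5. At g = 0.25 and ρ = 0.5 the order reverses: 56% if kept, 11% if lost. For TII to TIII the contrasts are d·g and d(1 + g), so the order holds for any positive g.

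**The alternative contrast: treatment received × period, over TII and TIII.** This compares the arms on the sum TII + TIII. The means are −d − s·d and −g·d, so its size is d(1 + s − g). The SD of the sum is √(2(1 + ρ)) = 1.732 at ρ = 0.5, and the standard error is 1.732 × √(2/64) = 0.306. At g = 1:
- kept: 0.50/0.306 = 1.63, rejected 37%
- half lost: 0.25/0.306 = 0.82, rejected 13%
- fully lost: 0, rejected 5%

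This moves in the stated direction. It cannot, however, tell lasting benefit from a weaker effect in group 2: s = 0.5 with g = 1 gives 0.5 × 0.5 = 0.25, and s = 0 with g = 0.5 also gives 0.5 × 0.5 = 0.25.

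**The case against.** The strongest defence is the carryover sentence itself. Group 1 has MBCT and then usual care; group 2 has usual care and then MBCT; outcomes are taken after each period. That is laid out like a two-sequence, two-period design without washout, and persistence of the MBCT effect into the later usual-care period is what carryover means. If treatment group meant the condition received in each period, rejection would become likelier as gains last, as the last calculation shows. A reader might infer that no coding of the model could support maintenance, or that carryover has no place in this design. Neither inference stands.

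What remains is that the article does not describe that model. Groups 1 and 2 are the fixed randomised arms throughout, and no treatment indicator that changes with period is defined. Even if one were intended, power would be 37% with gains fully kept (about 51% with adjustment for TI), and the reading would depend on equal benefit in both arms.

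Three further points are fair. The article speaks of support, not proof. The TI-to-TIII ordering is conditional on g. A reader might also infer that a relapse would certainly be reported as sustained benefit; analysts who looked at the sign and the group means could notice it, though the rule does not tell them to. The choice of coding is often left to a fuller document, but here the article states the inference itself, and on the natural reading that inference is wrong.

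**Conclusion.** The point holds for the model as naturally read, with group as randomised arm. Rejection of group × time does not indicate that group 1 kept its gains. With 64 per arm, d = 0.5, equal benefit and correlation 0.5, it is likelier when the gains are lost than when they are kept: 80% against 5% for TI to TIII, and over 99% against 80% for TII to TIII. The TI-to-TIII ordering needs group 2 to gain more than about half as much as group 1. Both arms receive the same programme, so equal benefit is the natural planning case.

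The defect is confined to hypothesis 3. The week-8 primary comparison is untouched. It still needs correcting, because the stated rule can reverse the conclusion on a declared aim of the trial.

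**What to change.** 1. Remove the statement that rejecting the interaction supports sustained effects, and the sentence equating that test with a carryover assessment.
2. Base hypothesis 3 on group 1's estimated TII-to-TIII change from the same mixed model, with a 95% confidence interval. Preferably judge it against a margin for acceptable worsening that the sponsor sets in advance.
3. Report group 1's TI-to-TIII change beside it.
4. State that no untreated comparator exists at TIII, so this is a within-group, non-randomised estimate.
5. Keep group × time for the TI-to-TII comparison (hypotheses 1 and 2).

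The cost is a change of wording and, if adopted, one margin. No extra visits or data are needed. The downside is that the maintenance claim is openly described as uncontrolled, which the design already makes it.

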### Potential Bias

It is possible that participants who choose to participate in this study could be more motivated than those who choose not to participate. Participants who are lost to follow-up after randomization could also affect the comparability of the groups.

### Ethical Considerations

This study was approved by the Institutional Review Boards (IRBs) at Greenville Health System and Clemson University (1852922; Pro00092709). All participants will provide written informed consent before participating in this study. This will be collected and safely stored by one of the clinical data collection team members.

### Dissemination

The IRB at Clemson University and Prisma Healthcare System have approved this study. Some of the topics we will discuss are personal and may be upsetting to some participants. If participants experience distress and need treatment, a licensed clinical psychologist or psychiatrist will be contacted immediately. If required, we will provide a list of referral sources for participants who need additional treatment. In the event of physical injury, we will follow emergency procedures for the facility from which the participants are recruited. If an adverse event occurs, a member of the research team will reach out to the affected participant within 24 hours. Subsequently, a meeting will be convened by the research team to discuss the cause of the adverse event and if any modification to this study needs to be made. If any modification needs to be made to the trial protocol, a formal amendment will be submitted to the IRB for approval.

